**Methods and design:**

This is a 4-week prospective observational study of 450 participants with established ASCVD or high cardiovascular risk with or without T2D and without previous SGLT2i medication undergoing exercise therapy during inpatient rehabilitation in a single center in Switzerland. Upon admission, participants are categorized into 3 groups of 150 participants each according to their glycemic control. Group I consisting of participants with inadequately controlled T2D defined as mean fasting plasma glucose (FPG) of ≥7 mmol/L, who are consequently administered new treatment with an SGLT2i. Group II comprises of participants with adequately controlled T2D with mean FPG of <7 mmol/L requiring no antidiabetic medication change. Group III consists of participants with no diabetes and mean FPG of ≤ 5.5 mmol/L. Primary outcomes are 6-min walk distance and rate of perceived exertion. Secondary outcomes are echocardiographic parameters (left ventricular mass index; global longitudinal strain average; end-diastolic volume), fatigue, muscle, metabolic, and anthropometric measures.

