### Study group categories

Glycemic control was assessed within the first 3 days upon admission by measurement of fasting plasma glucose (FPG) with the widely used diagnostic cut-off of ≥7 mmol/L employed to define inadequate glycemic control (33, 36). Hemoglobin A_1c_ (HBA_1c_) testing was equally done in all participants upon admission but was not used to define inadequate glycemic control in this cohort to circumvent the bias linked to participants with conditions that affect erythrocyte turnover such as acute bleeding and/or erythrocyte transfusion during the acute hospitalization prior to rehabilitation (33). HbA_1c_ was however used as one of the parameters to distinguish participants with diabetes or impaired glucose metabolism from those with normal glucose metabolism as described below.

Depending on their glycemic control upon admission and following guideline recommendations, participants were categorized to one of three groups using clinically defined cut-off categories of FPG levels as follows (11):

Group I: Participants with inadequately controlled T2D defined as mean FPG of ≥7 mmol/l within the first 3 days upon admission under other standard of care medication, who were afterwards administered *de novo* SGLT2i treatment; namely either canagliflozin 100 mg, or dapagliflozin 10 mg, or empagliflozin 10 mg once daily, with the choice of which of the SGLT2is being at the discretion of the individual treating physician,

Group II: Participants with adequately controlled T2D, previous diagnosis of T2D or use of antidiabetic medication, with mean FPG <7 mmol/L; and participants with impaired fasting glycemia (IFG) or pre-diabetes, defined as mean FPG of 5.6–6.9 mmol/L and HbA_1c_ levels of 5.7–6.4 % (15, 33), under other standard of care treatment and no SGLT2i,

Group III: Participants with no previous diagnosis of T2D or use of antidiabetic medication and normal glucose metabolism defined as FPG of ≤ 5.5 mmol/L under other standard of care treatment and no SGLT2i were included as a reference group as previously described in the meta-analysis of prospective studies on diabetes mellitus, FPG, and risk of vascular disease (11).

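### Group II is labelled adequately controlled diabetes, but its definition also admits people with pre-diabetes, and the HbA1c rule that separates the groups is inconsistent

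*Protocol article*

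**What the plan says.** **Labels.** The abstract (Methods and design) states: "Group II comprises of participants with adequately controlled T2D with mean FPG of <7 mmol/L requiring no antidiabetic medication change". Pre-diabetes is not mentioned there. The abstract's objectives, the fourth aim at the end of the Introduction, and Study design all name the middle level of the analysed contrast as diabetes with adequate control, set against inadequately controlled diabetes plus a new SGLT2i on one side and no diabetes on the other. The second aim concerns change in patients with T2D and adequate control.

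**Operative definition.** Under Study group categories, Group II has two parts. The first is "Participants with adequately controlled T2D, previous diagnosis of T2D or use of antidiabetic medication, with mean FPG <7 mmol/L". The second is "and participants with impaired fasting glycemia (IFG) or pre-diabetes, defined as mean FPG of" 5.6–6.9 mmol/L and HbA1c 5.7–6.4 %.

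**HbA1c.** The same section says that HbA1c "testing was equally done in all participants upon admission but was not used to define inadequate glycemic control in this cohort", because bleeding or transfusion before rehabilitation can bias it. It then says HbA1c was nevertheless "used as one of the parameters to distinguish participants with diabetes or impaired glucose metabolism from those with normal glucose metabolism as described below". Group III is then given as "Participants with no previous diagnosis of T2D or use of antidiabetic medication and normal glucose metabolism defined as FPG of" at most 5.5 mmol/L, with no HbA1c limit.

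**Analysis.** Data analyses lists diabetes duration among the covariates. It plans sensitivity analyses for other influential variables, and subgroups by ASCVD entity, gender, age and other factors. It names no analysis that separates T2D from pre-diabetes within Group II.

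**The concern.** The three-level group factor is the study's main exposure. A person with pre-diabetes, no T2D diagnosis and no antidiabetic drug belongs by the plain meaning of the labels to the no-diabetes level. The definition codes that person to the level called diabetes.

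Three results are affected:

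- The within-group change under the second aim would be reported for T2D but computed in a mixture.
- I vs II would differ by diabetes status, as well as by glycemic control and new SGLT2i treatment.
- II vs III would no longer compare adequately controlled diabetes with no diabetes.

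The adjustment set does not repair this. Diabetes duration has no natural value for the pre-diabetic members of Group II.

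Separately, if the boundary between impaired and normal metabolism is not fixed, two analysts could place the same participant in different groups.

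**Working it through.** **1. Label against definition.** The label requires diabetes. The second part of the Group II definition requires only an FPG and HbA1c pattern. Eligibility criteria determine T2D by self-report verified in records, current treatment, or FPG ≥7 mmol/L and symptoms with random glucose ≥11.1 mmol/L. FPG of 5.6–6.9 with HbA1c of 5.7–6.4 % meets none of these by itself. Group II is therefore a mixture.

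**2. Where the written rules place people with no T2D diagnosis and no antidiabetic drug.** The pre-diabetes wording can be read conjunctively (both limits needed) or respectively (IFG by FPG, pre-diabetes by HbA1c).

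| FPG (mmol/L) | HbA1c (%) | Conjunctive reading | Respective reading |
|---|---|---|---|
| ≤5.5 | <5.7 | III | III |
| ≤5.5 | 5.7–6.4 | III | II by HbA1c, but also meets the FPG line of III |
| ≤5.5 | ≥6.5 | III | III by its FPG line |
| 5.6–6.9 | <5.7 | no group | II |
| 5.6–6.9 | 5.7–6.4 | II | II |
| 5.6–6.9 | ≥6.5 | no group | II |

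The conjunctive reading leaves two cells unassigned. The respective reading fills them but makes one cell fit two groups. Under either reading, undiagnosed people with HbA1c ≥6.5 % and FPG below 7 are never assigned as people with diabetes, although HbA1c is said to help identify diabetes.

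**3. Size of the distortion.** Let *f* be the pre-diabetes share of Group II and *D* the difference in mean 6-MWD change between its T2D and pre-diabetes members. The Group II mean is displaced from its T2D-only value by *f* × *D*. The protocol gives neither quantity.

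As an illustration only, take *f* = 10–40 % (15–60 of 150 people) and *D* = 12 m. The displacement is then 0.10 × 12 = 1.2 m to 0.40 × 12 = 4.8 m. Dividing 4.8 m by 12 m returns the assumed 40 %, so that ratio carries no information about this trial.

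**4. Power cost of a T2D-only Group II.** Inputs from Sample size: improvement 80 m with SD 40 m, target difference 15 %, 150 enrolled per group, 85 % completing. The base of the 15 % is not stated; taking it as 80 m gives 0.15 × 80 = 12 m, which is an assumption.

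On that base the stated 130 per group for 80 % power is not reproduced: the normal formula gives 175, and 130 gives about 68 %. That is a separate matter, but it explains why the starting point below is under 80 %.

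SE = 40 × √(1/n₁ + 1/n₂); power ≈ Φ(12/SE − 1.96).

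- Full groups: n₁ = n₂ = 150 × 0.85 = 127.5. SE = 5.01 m, power = Φ(0.44) ≈ 67 %.
- *f* = 10 %: n₂ = 135 × 0.85 = 114.75. SE = 5.15 m, power = Φ(0.37) ≈ 64 %.
- *f* = 40 %: n₂ = 90 × 0.85 = 76.5. SE = 5.78 m, power ≈ 55 %.

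**The case against.** **The inclusion is disclosed.** Study group categories states openly that pre-diabetes is in Group II. This stands: the fault is a mismatch between definition and label, not concealment. It goes beyond a shortened abstract, because the aims and the analysed factor carry the same label.

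**Group III ignores HbA1c.** A reader might infer this from the Group III line. The document does not support it. The preceding paragraph says HbA1c was "used as one of the parameters to distinguish participants with diabetes or impaired glucose metabolism from those with normal glucose metabolism", and Group III requires normal metabolism, so HbA1c may have been applied in practice. What can be said is that the section is inconsistent.

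**Some participants fit no group.** This also goes too far as a flat statement, since it depends on the conjunctive reading. The ambiguity itself is real under both readings.

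**The contrasts are associations.** The Discussion says the non-randomized design precludes causal conclusions and names selection by glycemic control as a threat. I vs II was never a clean SGLT2i comparison. This stands, but an association still needs a correctly named exposure, and the limitations do not mention diabetes status within Group II.

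**Room exists in the analysis plan.** Sensitivity analyses and subgroups by other factors could cover a T2D-only analysis. None is named, so there is no commitment to one.

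**Recode into four levels as the primary analysis.** This is tempting, but it would change the main exposure after data collection ended in September 2020. Making HbA1c alone decisive at the Group III boundary would also ignore the bleeding and transfusion bias that the section itself raises.

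**Conclusion.** The point holds as a mismatch between what Group II is called and who is in it. Followed as written, the plan yields a Group II change and I vs II and II vs III comparisons that do not match their stated meaning, and no named analysis separates T2D from pre-diabetes. This rests on the text alone.

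The HbA1c wording is inconsistent and the pre-diabetes definition ambiguous; both need one explicit rule. The documents do not show that Group III was formed without HbA1c, or that any enrolled participant was left unclassified.

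The size of the distortion, and its direction, cannot be derived. The 1.2–4.8 m range depends wholly on an assumed share of 10–40 % and an assumed 12 m difference between T2D and pre-diabetes. A reader might infer that up to 40 % of the target effect is lost; that figure only repeats the assumed share.

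**What to change.** 1. Keep the three enrolled groups, and name the middle level *adequately controlled T2D or pre-diabetes* in the abstract, objectives, aims, design and analysis.
2. Pre-specify an analysis with Group II restricted to documented T2D and the pre-diabetes members shown separately. Base any statement about adequately controlled diabetes on it. State whether it was specified before results were seen.
3. Reconcile the HbA1c sentence with the Group III definition. Say whether the pre-diabetes limits are joint or alternative, and give the assignment of every FPG/HbA1c combination, including undiagnosed HbA1c of 6.5 % or more with FPG below 7 mmol/L.
4. Report Group III restricted to HbA1c below 5.7 % as a sensitivity analysis, not as the main coding, because of the stated concern about bleeding and transfusion.
5. Report the number with pre-diabetes in Group II, so that readers can judge the mixture.

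**Cost.** FPG and HbA1c were measured in all participants at admission, so this is recoding and rewording only. The price is a smaller T2D-only group. On the assumptions shown, power for 12 m falls from about 67 % to 64 % at a 10 % pre-diabetes share and to 55 % at 40 %. The estimate should therefore be read with its confidence interval.

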Given this background, the main aims of this study are firstly, to investigate the changes in physical performance and glycemic control 4 weeks after initiation of guideline-directed medical therapy of an SGLT2i and exercise therapy in patients with established ASCVD or high cardiovascular risk and T2D with initial inadequate glycemic control; secondly, to investigate the changes in physical performance and glycemic control 4 weeks after exercise therapy only in patients with established ASCVD or high cardiovascular risk and T2D with adequate glycemic control; thirdly, to investigate the changes in physical performance 4 weeks after exercise therapy only in non-diabetic patients with established ASCVD or high cardiovascular risk; and fourthly to investigate the cross-sectional and longitudinal association of glycemic control at baseline and new guideline directed antidiabetic treatment (inadequate glycemic control and diabetes + new SGLT2i vs adequate glycemic control and diabetes vs. no diabetes) with physical performance and other outcomes influencing physical performance (secondary outcomes), in patients with established ASCVD or high cardiovascular risk after adjusting for baseline covariates.

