## Methods and analysis

### Study design

The PUSH is a real-world, 4 week prospective, three-arm observational study of patients with established ASCVD or high cardiovascular risk with and without T2D undergoing regular exercise therapy during inpatient rehabilitation in a single center in Switzerland. Employing a multi-group design and a two-step analytic approach, the study investigates the changes in physical performance (and glycemic control) in 3 categories of glycemic control after 4 weeks. Furthermore, the associations between the 3 categories of glycemic control and new guideline directed antidiabetic treatment (inadequate glycemic control and diabetes + new SGLT2i vs. adequate glycemic control and diabetes vs. no diabetes) with physical performance are evaluated in cross-sectional and prospective analyses. A flow chart of the study is shown in Figure 1.

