#### Eligibility criteria

All consecutive patients with established ASCVD or high cardiovascular risk with or without T2D who met the inclusion criteria summarized below were prospectively enrolled as from 1 January 2018 and data collection lasted until 30 September 2020. Individuals below 40 years of age upon admission were excluded due to the low incidence of ASCVD in people under 40 years (32). For participants with T2D, T2D was determined by self-report with verification of medical records, current treatment or FPG ≥ 7 mmol/L and symptoms of hyperglycemia with random plasma glucose ≥ 11.1 mmol/L (33). Individuals who had a clinical history strongly suggestive of type I diabetes were excluded.

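### Group II is labelled adequately controlled T2D but also takes in people with impaired fasting glycemia or pre-diabetes, and no named analysis separates the two

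*Protocol article*

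**What the plan says.** Study group categories in the protocol article gives Group II two parts. The first is "Participants with adequately controlled T2D, previous diagnosis of T2D or use of antidiabetic medication, with mean FPG <7 mmol/L". The second is "and participants with impaired fasting glycemia (IFG) or pre-diabetes", with a mean FPG of 5.6–6.9 mmol/L together with HbA1c of 5.7–6.4%. Both parts are without an SGLT2i.

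Other sections describe the same group as T2D only:

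- Abstract, Methods and design: "Group II comprises of participants with adequately controlled T2D with mean FPG of <7 mmol/L requiring no antidiabetic medication change".
- Introduction, second aim: "exercise therapy only in patients with established ASCVD or high cardiovascular risk and T2D with adequate glycemic control".
- Study design, the contrast to be analysed: "inadequate glycemic control and diabetes + new SGLT2i vs. adequate glycemic control and diabetes vs. no diabetes". The abstract's Objectives and the fourth aim use the same three labels.

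Eligibility criteria sets out who counts as having T2D: "T2D was determined by self-report with verification of medical records, current treatment or FPG ≥ 7 mmol/L", the glucose route also requiring symptoms and a random plasma glucose of at least 11.1 mmol/L.

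Data analyses lists model covariates (age, sex, BMI, waist circumference, diabetes duration, cardiovascular history) and subgroups (type of ASCVD, gender, age group, and an open-ended remainder). T2D versus pre-diabetes within Group II is not named in either list.

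**The concern.** One of three arms is not the population that the objectives attach to it. Three results are affected.

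- **Aim 2.** The pre-post change in Group II averages people with and without T2D, in a ratio that nobody planned. It cannot be quoted as the change in adequately controlled T2D.
- **II versus III.** This is labelled diabetes against no diabetes, but part of the diabetes side has no diabetes. If those members respond more like Group III than like T2D, the contrast is diluted.
- **I versus II.** This is the comparison most likely to be read for the SGLT2i. Group I is entirely T2D and Group II is not, so diabetes status enters a comparison that already differs in glycemic control and drug. The Introduction says that T2D limits physical performance even when glycemia is adequately controlled, so by the article's own rationale the mix bears on the primary outcomes.

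**Working it through.** **1. Do the second-part members of Group II have T2D?** The definition in Eligibility criteria has three routes: a verified self-reported history, current treatment, or FPG of at least 7 mmol/L with symptoms and high random glucose. Anyone with a previous diagnosis or antidiabetic medication already belongs to the first part of Group II. The second part has FPG of 5.6–6.9 mmol/L, which is below 7. It meets none of the three routes. The contradiction with the abstract, aim 2 and the contrast label therefore needs no arithmetic.

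**2. The plan's own figure.** Sample size gives an improvement of 80 ± 40 m, an additional 15%, 80% power, two-sided 5%, and 130 per group. Taking 15% of 80 m = 12 m and SD 40 m:

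n = 2 × (1.960 + 0.842)² × 40² / 12² ≈ 175 per group.

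The stated 130 is not reproduced on this base. It corresponds to a difference of 40 × 2.802 × √(2/130) = 13.9 m. That mismatch is a separate matter and this point does not rest on it, but it is why the starting power below is 68% and not 80%.

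**3. Dilution of II versus III (illustration).** Assumptions:

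- true T2D versus no-diabetes difference 12 m;
- SD 40 m and 130 analysed per group;
- a share p of Group II is pre-diabetic (p is not in the article);
- pre-diabetic members carry a fraction r of the T2D difference, where r = 0 means that they respond like Group III.

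Pooled difference = 12 × [1 − p(1 − r)], with SE = 40 × √(2/130) = 4.96 m.

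T2D-only difference = 12 m, with SE = 40 × √(1/(130(1 − p)) + 1/130).

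Power = Φ(difference/SE − 1.96).

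| p | Pooled difference, r = 0 | Pooled power, r = 0 | T2D in Group II | T2D-only SE | T2D-only power |
|---|---|---|---|---|---|
| 0 | 12.0 m | 68% | 130 | 4.96 m | 68% |
| 20% | 9.6 m | 49% | 104 | 5.26 m | 63% |
| 40% | 7.2 m | 31% | 78 | 5.73 m | 55% |

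Starting from 13.9 m, where 130 per group has 80% power, the pattern is the same: at p = 20%, 61% pooled and 75% T2D-only.

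**4. How much depends on r.** At p = 20% and r = 0.5 the pooled difference is 12 × 0.9 = 10.8 m. Pooled power is then 59%, against 63% for T2D-only. The two are equal when [1 − 0.2(1 − r)] / 4.96 = 1 / 5.26, so 1 − 0.2(1 − r) = 0.943 and r ≈ 0.71. Above about 71% pooling has the higher power, and at r = 1 nothing is lost by pooling.

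**The case against.** The strongest case for the plan is that the composition of Group II is openly stated. Participants are sorted by glycemic control, HbA1c is used to tell diabetes or impaired glucose metabolism from normal metabolism, and Group III is a normal-glucose reference. Placing impaired fasting glycemia in the middle group follows that logic. This stands: nothing is concealed, and the grouping itself is a defensible choice. It does not rescue the labels, because the aims and the contrast speak of diabetes and not of impaired glucose metabolism.

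A second defence is that Data analyses allows further unnamed subgroups and sensitivity analyses for other influential variables, and adjusts for diabetes duration. None of these commits to separating T2D from pre-diabetes, and the article does not say what duration is assigned to people without diabetes. A fuller plan may settle this, but the conflict between the group definition and the aims is on the face of the article.

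Third, the size of the harm is hypothetical. The share is not given. The 12 m has no source as a diabetes effect: the 15% is taken from a study that the article describes elsewhere as an empagliflozin pilot. Full dilution is the extreme case. All of this stands, so the power figures are only an illustration.

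Fourth, the Discussion already names selection by glycemic control as a threat and rules out causal conclusions. That tempers the I–II point, but it does not mention that the comparator is partly non-diabetic.

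A reader might also infer that the third aim, set in "4 weeks after exercise therapy only in non-diabetic patients with established ASCVD or high cardiovascular risk", loses part of its population to Group II. The documents give little support for that: the abstract and Study group categories both limit Group III to FPG of 5.5 mmol/L or less, so the restriction is declared consistently and only the aim's wording is broader.

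**Conclusion.** The inconsistency is real and certain. People without T2D by the article's definition are in a group that the abstract, aim 2 and the three-way contrast call T2D or diabetes, and no named analysis separates them. As written, the Group II pre-post result is not a T2D result, and the II–III and I–II contrasts mix diabetes status in an unknown ratio.

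The numerical cost is not certain. A fall from 12 m to 9.6 m, and from 68% to 49% power, requires a 20% share and pre-diabetic members who respond exactly like Group III. A halfway response gives 59%, and a T2D-like response gives no loss.

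Two stronger readings go too far. One is that the diabetes contrast necessarily shrinks by the pre-diabetic share, which holds only under the full-dilution assumption. The other is that aim 2 cannot be answered at all: FPG, HbA1c, medical history and medication are recorded at baseline, so the T2D members can be identified.

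**What to change.** 1. For aim 2 and every contrast labelled diabetes or T2D, specify an analysis of Group II restricted to participants who meet the article's own T2D definition.
2. Show the participants with impaired fasting glycemia or pre-diabetes as a separate stratum.
3. Report the pooled Group II alongside, under an accurate label such as adequately controlled T2D or pre-diabetes.
4. Report how many Group II participants have T2D. The planned 150 is the size of the whole group.
5. Reconcile the abstract (Objectives, Methods and design), the aims in the Introduction, Study design and Study group categories.

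**Cost.** One stratum variable built from data already held, and some wording. Intervals in the T2D-only contrasts will be somewhat wider: at an assumed 20% share the standard error rises from 4.96 to 5.26 m (about 6%), and at 40% to 5.73 m (about 15%). Data collection ended in September 2020, so the T2D-only analysis should be declared as an addition made after data collection, with the pooled group as defined still reported.
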